## Abstract

Background: Arteriovenous fistula (AVF) is the preferred vascular access option for hemodialysis (HD). The latter requires a remodeling process called maturation that can take up to 3 months. Maturation failure is a frequent complication associated with significant morbidity. The prevalence of antiphospholipid antibody (aPL) positivity in HD patients is high and may result in thrombosis of the vascular access. Recently, aPL persistent positivity has been associated with AVF maturation failure in a retrospective study including 116 patients. Methods: We are conducting an observational prospective cohort study aiming to evaluate this association. Included patients are planned for AVF creation, aged over 18 years old, and have an interpretable aPL assay confirmed at 12 weeks and without any other innate or acquired thrombophilia or inflammatory disease. Primary endpoints will be the evaluation of AVF maturation clinically and by ultrasound. Secondary endpoints will focus on clinical outcomes other than AVF maturation (i.e., primary patency, thrombosis or stenosis, bleeding and hemodialysis adequacy parameters). Conclusions: This prospective observational cohort study aims to examine the possibly causative link between aPL persistent positivity and AVF maturation failure. This study was registered on ClinicalTrials.gov (ID number: NCT06112821).

## 1. Introduction

End-stage kidney disease (ESKD) is characterized by the need to initiate renal replacement therapy to control clinical, biological, and hemodynamic complications. Renal transplantation, peritoneal dialysis, and hemodialysis (HD) are currently the treatment options for ESKD. The Kidney Disease Outcomes Quality Initiative (KDOQI) guidelines advocate for the use of native arteriovenous fistula (AVF) as the primary option for establishing HD vascular access in patients with ESKD [1]. Arteriovenous fistula is associated with lower morbidity and mortality compared to arteriovenous grafts or the placement of a HD central venous catheter [2].

AVF creation consists of performing a surgical or endovascular anastomosis of a native artery to an adjacent native vein of the non-dominant superior limb. AVF creation encompasses the outflow vein structural changes characterized by an increased efferent vein diameter, thickness and blood flow [3,4]. This process, usually called “maturation”, takes place within 6 weeks to 3 months and is crucial for routine AVF puncture in HD [5]. Maturation failure of a native AVF is a frequent complication and is characterized by the absence of, or a delay of, maturation, defined either clinically or by using Doppler ultrasound (US) [3,6].

Antiphospholipid syndrome (APS) is an autoimmune disease characterized by the persistent positivity of at least one antiphospholipid antibody (aPL). It is an acquired thrombophilia that affects both the arterial and the venous vasculature. New classification criteria were released in 2023, based on a scoring system [7]. With respect to laboratory domains, the following antibodies are included: lupus anticoagulant (LA); the IgG or IgM anti-cardiolipin antibody (aCL); and the IgG or IgM anti β2 glycoprotein I (aβ2-GPI). Confirmation of a positive assay is mandatory at 12 weeks, leading to confirming the biological criterion. In the absence of any clinical criteria, aPL persistent positivity does not allow for the diagnosis of APS. It is interesting to note that the 2023 ACR/EULAR classification criteria no longer consider isolated positivity of IgM aCL and/or IgM aβ2-GPI [either at moderate titers (40–79 units/mL) or high titers (>80 units/mL)] as sufficient in order to classify a patient as having APS [7].

Although ESKD is rare in APS, the prevalence of persistent aPL positivity is higher in HD patients compared to the general population, and can reach more than 35% [8]. The reason for such a high prevalence of aPL positivity in HD is not well known. Several hypotheses have been proposed such as (a) molecular mimicry as a response to the exposure to microorganisms, endotoxins or HD membranes, or (b) a response to oxidation (i.e., cross-reactive immunoglobulins against epitopes of oxidized lipids) [8]. Nevertheless, aPL positivity has been inconsistently associated with AVF thrombosis [8,9,10,11]. Also, aPL positivity has been rarely associated with AVF stenosis [12] and intrastent restenosis [13]. Recently, our group published the first report of a significant association between aPL persistent positivity, and native AVF maturation failure as defined by US in a retrospective study including 116 HD patients [14]. The aPL positivity was a strong predictor of AVF maturation failure in multivariate analysis.

The aim of the present study is to confirm this association in a prospective cohort. The primary outcome of the study is to examine the possibly causative link between aPL persistent positivity and the occurrence of AVF maturation failure defined by the clinical approach combined with US.

Secondary outcomes will focus on clinical outcomes other than AVF maturation: functional primary patency and primary patency, time to AVF complications, AVF thrombosis or stenosis rates, bleeding complications rates and HD adequacy parameters.

In addition, in order to better understand the underlying pathophysiological mechanism of AVF maturation failure in aPL positive patients, we will perform blood analyses as well as an in vitro study using cultured immortalized human microvascular endothelial cells type 1 (HMEC-1).

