## 2. Materials and Methods

### 2.1. Design and Objectives

This is a monocentric observational prospective cohort study that aims to recruit a cohort of 100 newly created native AVF in CKD patients with a previous aPL profile determination before AVF creation and HD initiation.

The sample size calculation was based on the assumption that the expected maturation failure rate in the general population is 50%, and is 70% in the aPL positive group. With alpha = 0.05, 1-Beta = 90%, and a two-sided test, 96 patients are required to detect a significant difference. Thus, we plan to enroll and analyze 100 patients.

Surgical AVF creation is performed as per standard of care without procedural variations between the aPL+ and control groups, ensuring homogeneity in the approach. No perioperative treatments or clinical assessments are specified by the study protocol.

Institutional Review Board authorization was obtained from the Brugmann University Hospital Ethics Committee (Reference number: CE2022/113), in accordance with the Declaration of Helsinki. Written informed consent is obtained from patients before any inclusion procedure. This study was registered on ClinicalTrials.gov (ID number: NCT06112821), and the study was started on August 2023. The study protocol is illustrated in Figure 1.

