### 2.8. Statistical Analyses

The total expected sample size is assumed to be a minimum of 100 patients based on an average recruitment rate of 2 patients/month. Analyses will describe AVF clinical outcomes for patients with and without persistent aPL positivity, potential predictors of patient outcome. Analyses will use all available data, regardless of final sample size.

Data will be expressed as mean ± standard deviation (SD) for variables with a normal distribution or as median ± interquartile range (P25; P75). Student’s t-test will be used to compare the means of the quantitative variables following a normal distribution by group. The Mann–Whitney Wilcoxon test will be used to study the variation between two groups of variables following an asymmetric distribution. The significance level of the tests was 0.05 with odds ratios and 95% confidence intervals. Multivariate models will be performed through logistic regression for variables showing statistically significant differences between groups.

We will employ Kaplan–Meier survival analysis to estimate the probability of AVF primary patency and functional primary patency over time.

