**Figure 2 life-15-00168-f002:**
[figure not shown]
Pathophysiological hypothesis of aPL-associated AVF maturation failure. The first line represents the pathways implicated in the pathophysiology of APS and the second line represents the presentation of AVF maturation failure (either in the presence of thrombosis, stenosis or because of insufficient venous remodeling). The dashed arrows represent pathophysiological hypotheses that have not been studied in the literature, while the solid arrows represent associations described in the literature. MCP-1: Monocyte Chemotactic Protein 1, MMP: matrix metalloproteases, mTOR: mammalian Target of Rapamycin, NO: nitric oxide, TIMP-1: tissue inhibitor of metallo-proteinase-1.

**Table 1 life-15-00168-t001:** Baseline characteristics collected at the time of AVF surgical creation.

Parameters	
Demographics	Age
	Gender
	BMI (kg/m^2^)
	Ethnicity
	Smoking status
Treatments	Anti-platelet therapy
	ACE/ARBs
	Statins
	Erythropoietin
	Anticoagulation therapy
	Beta-blockers
Medical history	Etiology of CKD, histologically proven
	Diabetes mellitus
	Hypertension
	Coronary heart disease
	Stroke or TIA
	Ischemic heart disease
	Peripheral vascular disease
	Left ventricular ejection fraction
	Deep vein thrombosis (n, %)
	Other aPL related clinical features
Biological	Hemoglobin level
features	Platelet count, mean platelet volume
	Coagulation tests: activated PTT, fibrinogen, Prothrombine time
	Lipids
	c-reactive protein, ESR
	Nt-proBNP
Vascular access	Need for catheter before AVF use
parameters	AVF creation date, AVF type, surgical procedure information (type of anesthesia, artery and vein diameter, anastomosis diameter)
	Mapping details
	Perioperative complications: bleeding, local hematoma, other complications
	Pre-operative Flow mediated dilation of the brachial artery as a marker of endothelial dysfunction

ACE: angiotensin-converting enzyme inhibitors; ARB: angiotensin II receptor blockers; AVF: arteriovenous fistula; BMI: body mass index; CRP: c-reactive protein; TIA: transient ischemic attack.

**Table 2 life-15-00168-t002:** Primary and secondary outcomes.

Primary Outcomes	
AVF maturation	Defined 6 weeks after AVF creation, by US: AVF brachial artery blood flow > 600 mL/min, outflow vein diameter > 6 mm;

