	Defined clinically if cannulation is possible with two needles for at least 75% of HD sessions over a continuous 4-week period, including either a mean HD machine blood pump speed superior to 300 mL/min over four consecutive sessions or a measured urea Kt/V > 1.4, or a urea reduction ratio (URR) > 70%
Assisted maturation	Need for any intervention (e.g., ballon angiography, etc.) in order to promote maturation
Time to first AVF puncture	

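### The primary outcome is fixed inconsistently: one combined outcome in the Introduction, three primary rows in Table 2, and no rule joining the ultrasound and clinical definitions of maturation

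*Protocol article*

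**What the plan says.** The protocol article describes the primary outcome in four places.

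- **1. Introduction:** one primary outcome, "the occurrence of AVF maturation failure defined by the clinical approach combined with US".
- **Abstract:** a plural, "Primary endpoints will be the evaluation of AVF maturation clinically and by ultrasound".
- **2.1 Design and Objectives:** one maturation failure rate per group, 50% against 70%, with no definition attached: "With alpha = 0.05, 1-Beta = 90%, and a two-sided test, 96 patients are required to detect a significant difference".
- **Table 2, primary outcomes:** three named rows.
  - AVF maturation, with two definitions. The US one is "Defined 6 weeks after AVF creation, by US: AVF brachial artery blood flow > 600 mL/min, outflow vein diameter > 6 mm". The clinical one begins "Defined clinically if cannulation is possible with two needles for at least 75% of HD sessions over a continuous 4-week period" and adds a pump-speed, Kt/V or urea-reduction criterion. A semicolon separates the two.
  - Assisted maturation: "Need for any intervention (e.g., ballon angiography, etc.) in order to promote maturation".
  - "Time to first AVF puncture", with no further definition.

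Section 2.8 gives a general level: "The significance level of the tests was 0.05 with odds ratios and 95% confidence intervals". It does not say which primary outcomes are tested, or that each is tested separately.

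Two further facts matter. Section 2.2 admits only patients who have not yet started HD, and section 2.4 sets follow-up at one year from AVF creation.

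**The concern.** The study is meant to confirm an association reported in a retrospective cohort, so a reader must know in advance which result would count as confirmation. The article gives different answers in different places.

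The Introduction's combined outcome cannot be scored as written. Nothing says whether failure means failing both definitions or either one, or by when the clinical definition must be met. Different rules give different failure rates, so the 50% and 70% in the sample size cannot be attached to an endpoint.

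If several rows remain primary, a significant result on any one could be presented as the primary finding. The choice of rule or row could also be made after the data are seen.

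**Working it through.** **1. The plan's own figure.** Inputs from section 2.1: 50% against 70%, two-sided 0.05, power 90%. With equal groups and mean rate 0.60:

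n per group = [1.96 × √(2 × 0.60 × 0.40) + 1.2816 × √(0.50 × 0.50 + 0.70 × 0.30)]² / 0.20² = (1.358 + 0.869)² / 0.04 ≈ 124, or 248 in total.

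The stated 96 is not reproduced, either as a total or per group. That is a separate problem. What matters here is that the calculation takes one binary failure outcome and one test at 0.05, so it presupposes a single primary endpoint.

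**2. Passages side by side.**

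| Place | Number of primary outcomes | Rule joining US and clinical |
|---|---|---|
| Introduction | one | combined, rule not given |
| Section 2.1 | one failure rate per group | definition not given |
| Abstract | plural | not given |
| Table 2 | three rows; four if US and clinical are counted separately | semicolon only |

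**3. Effect of the missing rule.** Assume, for illustration only, that each definition fails in 50% of patients and that the two are not negatively associated.

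- Fails both: from 0.5 × 0.5 = 25% (independent) to 50% (fully concordant).
- Fails either: from 50% (fully concordant) to 1 − 0.5 × 0.5 = 75% (independent).

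The same patients could thus show a failure rate anywhere from 25% to 75%, depending on the rule and the concordance.

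**4. Timing.** US maturation is fixed at 6 weeks. The clinical definition needs a continuous 4-week run of HD sessions. To be complete at week 6, cannulation would have to begin by week 6 − 4 = 2. The Introduction puts maturation at 6 weeks to 3 months. Participants are not on HD at entry, so anyone who does not start HD within the year has no clinical value at all.

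**5. Error rate if each outcome were tested at 0.05.** This is conditional, because the article does not state it. For k independent tests the chance of at least one false positive is 1 − 0.95^k. Under any dependence it is at most k × 0.05.

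| k | Independent | Upper bound |
|---|---|---|
| 2 (US and clinical) | 1 − 0.95² = 9.75% | 10% |
| 3 (Table 2 rows as printed) | 1 − 0.95³ = 14.3% | 15% |
| 4 (US and clinical counted separately) | 1 − 0.95⁴ = 18.5% | 20% |

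With four equally correlated normal test statistics (simulation, 1,000,000 draws), the rate is 17.4%, 15.6%, 13.0% and 9.4% at assumed correlations of 0.3, 0.5, 0.7 and 0.9. The article gives no correlations.

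**The case against.** - **The Abstract and the Introduction can be read as agreeing.** Evaluating maturation clinically and by US may be the same thing as a clinical approach combined with US. This is fair for those two places. It does not explain the two further primary rows in Table 2 or supply the combination rule.
- **Multiplicity handling belongs in an analysis plan that is not shown.** This stands: the absence of an adjustment is not a finding. The contradiction between sections of the article is.
- **The aim, sample size and conclusion all concern maturation failure**, so assisted maturation or time to puncture would hardly carry the claim. This is a reasonable reading of the intent, and a reason to stop listing them as primary.
- **A US-only primary endpoint cuts against the design.** The retrospective study was already US-defined, this study adds the clinical approach, and the Discussion concedes that combining flow and vein diameter may have produced an artifact. This has force. The fix should therefore have the two US components reported separately and leave the combined endpoint open, provided it is fully specified.
- **The clinical definition is not wholly without time limits**, given its 4-week window and the one-year follow-up. True, but neither says when the outcome is assessed or by when it must be met.

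A reader might go further and infer four primary outcomes, each tested at 0.05, with an error rate of 18.5%. The article does not support that. Table 2 prints three rows, separate testing is not stated, and 18.5% is the value under independence rather than a ceiling. Aspects of one process are likely to be positively correlated, which lowers it.

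**Conclusion.** The inconsistency is in the text and does not depend on any unseen document: one outcome in the Introduction and the sample size, several in the Abstract and Table 2. The combined outcome also lacks an AND/OR rule and a clinical assessment time, and its clinical part cannot be scored in participants who do not reach HD within the year.

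The possible inflation of the error rate is secondary and conditional on separate testing at 0.05: about 10%, 14% or 18.5% for two, three or four independent tests, and about 9% to 17% for four at assumed correlations of 0.9 to 0.3. A single endpoint tested once keeps it at 5%. The matter should be settled before analysis.

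**What to change.** Before analysis, name one primary endpoint, tested once at two-sided 0.05.

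- **Natural choice:** US maturation failure at 6 weeks. It has a fixed time, can be assessed whether or not HD has started, and is how the association to be confirmed was defined. State that maturation requires both the flow and the diameter criterion, so that failure means at least one is not met. Report each component separately as well, given the Discussion's own caution about combining them.
- **If the combined endpoint is kept:** state the AND/OR rule, the assessment time for the clinical part, and how patients not on HD are handled.
- **Other outcomes:** move assisted maturation, time to first puncture and the remaining maturation definition to secondary outcomes, reported with 95% confidence intervals and no confirmatory claim.
- **Consistency:** make the Abstract, Introduction and Table 2 agree. State which definition the 50% and 70% rates come from; section 2.1 does not say, so they should not be assigned to the chosen endpoint without a source.

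The cost is wording in the protocol, and in the registration if it lists the outcomes in the same way. No new data are needed. The downside is that only one outcome carries the confirmatory claim.

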## 2. Materials and Methods

### 2.1. Design and Objectives

This is a monocentric observational prospective cohort study that aims to recruit a cohort of 100 newly created native AVF in CKD patients with a previous aPL profile determination before AVF creation and HD initiation.

The sample size calculation was based on the assumption that the expected maturation failure rate in the general population is 50%, and is 70% in the aPL positive group. With alpha = 0.05, 1-Beta = 90%, and a two-sided test, 96 patients are required to detect a significant difference. Thus, we plan to enroll and analyze 100 patients.

Surgical AVF creation is performed as per standard of care without procedural variations between the aPL+ and control groups, ensuring homogeneity in the approach. No perioperative treatments or clinical assessments are specified by the study protocol.

Institutional Review Board authorization was obtained from the Brugmann University Hospital Ethics Committee (Reference number: CE2022/113), in accordance with the Declaration of Helsinki. Written informed consent is obtained from patients before any inclusion procedure. This study was registered on ClinicalTrials.gov (ID number: NCT06112821), and the study was started on August 2023. The study protocol is illustrated in Figure 1.

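### The 96 patients stated for 90% power do not follow from 50% versus 70% maturation failure; with 50% as the aPL-negative rate, the planned 100 give about 53% power at best

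*Protocol article*

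**What the plan says.** Section 2.1 (Design and Objectives) gives the assumptions: "the expected maturation failure rate in the general population is 50%, and is 70% in the aPL positive group". From these it concludes: "With alpha = 0.05, 1-Beta = 90%, and a two-sided test, 96 patients are required to detect a significant difference". It continues: "Thus, we plan to enroll and analyze 100 patients".

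The 100 is a total over both groups. Section 2.1 says that the study "aims to recruit a cohort of 100 newly created native AVF in CKD patients", and section 2.8 (Statistical Analyses) gives it again as a total, this time on feasibility grounds: "The total expected sample size is assumed to be a minimum of 100 patients based on an average recruitment rate of 2 patients/month".

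Section 2.3 (Study Groups) divides the cohort into an aPL-positive and an aPL-negative arm. Under section 2.2 (Participants) patients enter whatever their earlier aPL status, so the split is not fixed by design. The calculation states no split and no aPL prevalence. The only prevalence figure is in the Introduction, where persistent positivity in haemodialysis patients is said to be higher than in the general population "and can reach more than 35" per cent.

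**The concern.** The sample-size statement gives both rates, the significance level, the sidedness and the power, so it can be checked directly. A 20-point difference around 60% normally needs well over 200 patients in two groups for 90% power, so 96 is too small by a wide margin.

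The comparator is also unclear. The 50% is attached to the general population, which includes aPL-positive patients, while the groups to be compared are aPL-positive and aPL-negative. The required number depends heavily on which of the two the 50% describes.

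The Introduction says that the study aims to confirm a retrospective association, and the Discussion says that confirmation could make aPL screening routine. A reader told that power is 90% would take a non-significant result as fairly strong evidence against a 20-point difference. If power is nearer one half, that inference is not justified.

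**Working it through.** **Inputs from section 2.1:** p0 = 0.50, p1 = 0.70 (difference d = 0.20), two-sided alpha 0.05 (z = 1.960), power 90% (z = 1.282), stated requirement 96, planned total N = 100.

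**Input not in the article:** the aPL-positive share s. I take 50% as a favourable bound, and 35% and 20% as assumptions. The 35% borrows the Introduction's figure for haemodialysis patients. The patients enrolled have not started haemodialysis, so their share is not established and may be lower.

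**Formula** (pooled two-proportion test). With pbar = s·p1 + (1−s)·p0:
- A = √[pbar(1−pbar)(1/s + 1/(1−s))]
- B = √[p1(1−p1)/s + p0(1−p0)/(1−s)]
- total N = [(1.960·A + 1.282·B)/d]²
- power at N = Φ[(d√N − 1.960·A)/B]

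**Step 1: the plan's own figure.** At s = 0.5, pbar = 0.60, A = 0.980 and B = 0.959. N = [(1.920 + 1.229)/0.20]² = 248, or 124 per group. The article's 96 is not reproduced.

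**Step 2: other methods, same rates, 1:1.**

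| Variant | Total |
|---|---|
| 90% power, two-sided, unpooled variance | 242 |
| 90% power, two-sided, arcsine | 248 |
| 90% power, two-sided, continuity-corrected | 268 |
| 90% power, one-sided | 202 |
| 80% power, two-sided | 186 |
| 80% power, one-sided | 148 |
| One-sample test against a fixed 50%, 90% power, two-sided | 62 |

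None gives 96. Read as 96 per group (192 in total), the power is 81%, and the planned total of 100 contradicts that reading.

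**Step 3: power with the planned 100, taking 50% as the aPL-negative rate.**

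| Share aPL-positive | Total for 90% power | Power at N = 100 |
|---|---|---|
| 50% | 248 | 53% |
| 35% | about 273 | 49% |
| 30% | about 296 | 45% |
| 20% | about 388 | 35% |

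At s = 0.5, for example: (0.20 × 10 − 1.960 × 0.980)/0.959 = 0.083, and Φ(0.083) = 0.53. Exact calculations agree: 55% (chi-square) and 46% (Fisher) at 50/50, and 51% and 45% at 65/35.

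**Step 4: what 100 patients can detect or estimate.** Against a 50% comparator, 90% power is reached at a difference of about 30 points at 1:1 and about 32 points at 35% positive. With 35 and 65 patients, the 95% confidence interval on a 20-point difference has a half-width of 1.96·√(0.21/35 + 0.25/65) = 0.194, about 19 points.

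**Step 5: the alternative reading, with 50% as the overall rate.** The aPL-negative rate is then p0 = (0.50 − 0.70·s)/(1 − s).

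| Share aPL-positive | Implied aPL-negative rate | Total for 90% power | Power at N = 100 |
|---|---|---|---|
| 40% | 36.7% | about 94 (96 with group sizes rounded up) | 92% |
| 39% | 37.2% | about 98 | 91% |
| 35% | 39.2% | about 116 | 85% |
| 30% | 41.4% | about 146 | 76% |
| 20% | 45.0% | about 249 | 52% |

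**The case against.** The strongest defence is the alternative reading in step 5. Taken literally, section 2.1 gives 50% as the rate in the general population. If that means all patients having a fistula created, the aPL-negative rate is below 50%, the true contrast exceeds 20 points, and a total near 96 does come out at about 39 to 40% positive. The Introduction's wording puts no ceiling at 35%, so such a share cannot be excluded. This part stands: it would be wrong to say that no reading reaches 96.

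It does not rescue the statement. It needs an aPL-positive share and an aPL-negative failure rate that the article never gives, and it is fragile: 85% power at a 35% share, 76% at 30% and 52% at 20%.

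A second point also stands. The 35% describes haemodialysis patients and is not a design assumption for this pre-dialysis cohort. The 49% power figure is therefore conditional, and should not be entered in the protocol as though the protocol had assumed it.

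A reader might also infer that 96 is the size of the aPL-positive arm mistaken for the total, since that arm comes to 95.6 at a 35:65 split. The document does not support this. The match depends on the chosen share (the arm is 88.8 at 30% and 103.6 at 40%), and other routes give the same number. One is the precision of a single 50% proportion to within 10 points: 1.96² × 0.25/0.10² = 96.04. The origin of 96 is unknown, and the error does not depend on it.

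Finally, section 2.8 says that the analyses will describe outcomes, and the Discussion foresees further exploratory or confirmatory studies. That tempers how a null result might be read, but leaves the power claim uncorrected.

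**Conclusion.** The statement is wrong as written and must be corrected. With 50% as the aPL-negative rate, 248 patients are needed at 1:1, about 2.6 times the stated 96 (248/96), and more at lower aPL-positive shares. Power with 100 patients is at most about 53% for any share up to one half. That bound rests only on the article's own rates and error levels. The figures of 49% and 35% rest in addition on assumed shares of 35% and 20%.

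Two stronger conclusions are not supported. The article does not show that power is 49%, because it fixes neither the share nor, unambiguously, the comparator rate. Nor is the recruitment-rate sentence in section 2.8 an error: it gives a feasibility basis for 100, which may stay beside a correct power statement. The defect is a numerical result that does not follow from its printed inputs, so an unseen full protocol or analysis plan cannot make that sentence true, although it might show which inputs were used.

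**What to change.** Keep the planned 100 patients and change section 2.1 as follows:

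- Withdraw the statement that 96 patients give 90% power.
- Name the aPL-negative group as the comparator, and state its assumed failure rate and the assumed aPL-positive share.
- Restate power for 100 patients over a plausible range of shares. For 50% versus 70%, this is about 53% at 1:1, 49% at 35% positive and 35% at 20%. Alternatively, give the difference detectable with 90% power: about 30 points at 1:1 and 32 points at 35% positive. If the sponsor meant 50% as the overall rate, the implied aPL-negative rate and the matching power figures belong here instead.
- State that the group difference will be reported with its 95% confidence interval, and that a non-significant result will not be read as absence of association.

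The cost is wording only, with no added patients or procedures. The downside is that the stated power becomes less favourable.
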